## Methods

### Design

A multicenter, international longitudinal observational study of patients commencing palliative RT for CIBP.

### Study objectives

The primary aim of the PRAIS study is to investigate clinical and biomarker predictors of pain response after palliative RT for CIBP. In the secondary analyses of this longitudinal study we will explore association between inflammation and pain intensity, cachexia, and depression in patients with CIBP that undergo palliative RT, factors associated with development of cachexia in one-year follow up and correlation between pain intensity and depression (Fig. 1).

**Fig. 1 Fig1:**
[figure not shown]
Study objectives with Research Questions (RQ)

### Study population

#### Patients to be screened for participation

All patients admitted to palliative RT for bone cancer pain is eligible for screening.

#### Inclusion criteria

Verified cancer diagnosis, including hematological malignancies (based on radiological, histological, cytological or operative evidence)Bone metastases verified either by x-ray, bone scan, computer tomography (CT) or magnetic resonance imaging (MRI)Patients that are about to undergo RT with palliative intent for painful bone metastasesRT to be administered within 1 week after baseline observations are obtainedAge ≥ 18 yearsPatient able to comply with trial procedures

#### Exclusion criteria

Pathological fracture in long bonesPatients not consenting to participate in the studyOn-going RT or RT administered within the last 4 weeksPatients who are not able to follow the trial proceduresPrevious participation in this study

### Measurements

#### Timeline

The patients will be assessed at baseline and 3, 8, 16, 24 and 52 weeks after RT.

#### Clinical variables

At inclusion the following information will be collected (variables included as independent variables in the primary analyses are denoted with an asterisk): Age^*^, gender^*^, ethnicity, height, comorbidity^*^ (Charlson Comorbidity Index) [51], Karnofsky performance status^*^ [52], living situation, educational level, alcohol use, smoking status^*^, type of department (palliative care unit, surgical ward, general oncology ward, out-patient clinic, other), oncological history related to the current cancer disease (tumor diagnosis^*^, time since cancer diagnosis^*^, presence of metastases other than bone^*^, osteolytic metastasis at each planned site for RT^*^, soft tissue expansion at each planned radiation site^*^, previous and on-going anti-cancer treatment: (RT, surgery, chemotherapy, hormonal treatment, other interventions – for the primary analyses current oncological treatment other than RT (Y/N)^*^), planned RT (fractions^*^, total dose^*^ and anatomical region; narrow to radiation location in weight bearing bone (Y/N) for the primary analyses^*^, re-irradiation, previous pain treatments (duration of opioid treatment and previous unsuccessful trials with other opioids) and medications and doses for the previous 24 h (for the primary analyses we will include opioid dose in oral morphine equivalents last 24 h^*^and steroids^*^). In addition, an objective measurement of lean body mass, measured by CT scan of L3 and/or Th4 vertebrae will be performed at baseline.

At both baseline and at all follow-up visits the following self-reports will be collected: Health related quality of life (EORTC QLQ-C15 PAL) [53] (for the primary analyses trouble sleeping^*^, nausea^*^ and constipation^*^ will be included as variables), nutritional status (PG-SGA) [54], weight, overall and site specific average and worst pain last 24 h (BPI) [55] (for the primary analyses “worst pain last 24h”^*^), pain at rest and at movement from each planned irradiated site [56] (for the primary analyses we will use the variable that reflects worst pain at the irradiated site at baseline^*^) and depression^*^ (PHQ9) [57]. Specific questions related to episodic pain^*^ and self-report neuropathic symptoms and signs^*^ (LANSS) [58] will be asked at baseline and after 3 and 8 weeks.

Data on history of hospitalizations, changes in medications, new cancer treatment, treatment for hypercalcemia, new pathological fractures or spinal cord compression since last visit will be obtained at all follow-up visits (Table 1).

**Table 1 Tab1:** Flow chart for registrations

	Time of assessment					
	Inclusion	3 W	8 W	16 W	24 W	1 YR
Screening for inclusion	X					
Demographics, cancer history, planned RT, previous pain therapy	X					
New cancer related incidents		X	X	X	X	X
Current use of medications	X	X	X	X	X	X
Weight	X	X	X	X	X	X
Performance status	X	X	X	X	X	X
CT scans for body composition (if available)	X	X	X	X	X	X
PG-SGA	X	X	X	X	X	X
Pain registrations	X	X	X	X	X	X
QLQ-C15 PAL	X	X	X	X	X	X
LANSS	X	X	X			
Episodic pain questions	X	X	X			
PHQ9	X	X	X	X	X	X
Blood samples for clinical chemistry	X	X	X	X	X	X
Blood samples for biomarkers	X	X	X	X	X	X
Blood samples for genetics	X					

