### Power consideration

The sample size is based upon the primary outcome; response to RT for pain [18]. The analyses plan includes up to 29 independent clinical variables (see previous sections for variables marked with an asterisk.) A full statistical estimate of sample size requires knowledge of the variance-covariance matrix, which was not available at the planning stage of this study. Therefore, the widely-used rule of thumb of 10 x number of variables was adopted. This reasoning resulted in a sample size of 290. Based upon experience, interactions will arise which increases the needed number of patients, and up to 20% of patients were expected to be lost to follow-up. To account for this, the number of needed patients was set to 600. The original protocol plan was to include a validation sample of 1/3 of patients resulting in a total number of 1000 included patients. But because of slow recruitment, we had to close the study after 600 recruited patients, and the analyses will therefore be performed without the planned validation sample.

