*Statistical method*: Clinical variables (see previous chapter) and CRP will be included in a multivariate logistic regression model to predict potential factors for response to RT. The model will be adjusted by study centre. Regression diagnostics will be performed for all analyses adding interactions terms if necessary. Significant variables from the multivariable model will be presented as a response-score to determine the likelihood of response to RT. Second, we will perform analyses on inflammatory biomarkers and bone biomarkers correlated with response to RT. Only inflammatory biomarkers and bone biomarkers with levels of serum concentrations above the detection threshold and which have a variability between measurements will be analysed with a multivariate logistic regression model with response to RT as the dependant variable. Finally, an integrated regression model with response to RT including both the significant clinical variables and significant biological biomarkers will be conducted if appropriate based on results from the previous analyses.

**Research question 2:** Which inflammatory biomarkers are associated with change in pain intensity in patients with CIBP?

*Objective*: To investigate the correlation between pain intensity and inflammation. Patients included in the PRAIS study all have CIBP and will receive a standardized intervention expected to give pain relief in about 60% of the patients. This study can explore if there is a longitudinal relationship between changes in pain intensity and the detected level of inflammatory biomarkers.

*Outcome*: Serum concentrations of inflammatory biomarkers as described above associated with changes in pain intensity as measured by average pain intensity and worst pain intensity last 24 h (NRS 0–11) for a maximum of 1 year follow-up.

*Statistical method*: Longitudinal data analysis with repeated measurements using a liner mixed effect model or generalized estimating equation (GEE).

**Research question 3:** Which inflammatory substances are associated with cancer cachexia?

*Objective*: To gain insight into the role of inflammation in cancer cachexia.

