## Discussion

Clinical trials in cancer are mostly carried out to evaluate and compare different treatment strategies, medications and interventions. Whiles the effect of RT to treat CIBP is well documented, there is limited information about which characteristics that differs among responders versus non-responders. To achieve reliable predictors for treatment response, studies with large patient materials that obtain follow-up visits are needed. In this study, detailed clinical information, inflammatory and bone biomarkers will be collected before RT. These are all data and analyses that could be included in routine clinical practice to better select patients likely to have RT response. This can reduce the administration of non-efficacious RT. Patients will benefit from not spending time on futile treatment and not risking adverse effects related to RT as well as not delaying alternative pain treatments.

Our research group has in the last decade published several papers on cancer pain and the relationship between pain and other cancer symptoms to improve cancer pain classification [59–61]. International collaboration have also developed the Edmonton classification for cancer pain [56, 62]. The PRAIS study will include a large cancer patient population with advanced, but not terminal, cancer disease that will be used to investigate which clinical characteristics and biomarkers are associated with other cancer related symptoms. We will explore the longitudinal associations for pain, depression and cachexia with clinical characteristics, and biomarkers.

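### Fractions and total dose enter the primary model as two separate, probably strongly correlated predictors, and selecting score items by single-coefficient significance can lose a real association between RT regimen and response

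*Protocol article*

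**What the plan says.** In the protocol article, Measurements, Clinical variables, the rule for the primary model is that "variables included as independent variables in the primary analyses are denoted with an asterisk". The same paragraph lists "planned RT (fractions^*^, total dose^*^ and anatomical region", with separate asterisks on fractions and on total dose. It does not say whether fractions are used as a count or as single versus multiple, and it gives no regimens.

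Under Outcome and statistical analyses, research question 1, "Clinical variables (see previous chapter) and CRP will be included in a multivariate logistic regression model", with adjustment for study centre. The selection rule follows: "Significant variables from the multivariable model will be presented as a response-score to determine the likelihood of response to RT". On model checking, the section says "Regression diagnostics will be performed for all analyses adding interactions terms if necessary". It states no combined regimen variable, no joint test and no rule for collinear predictors.

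Under Power consideration, "The analyses plan includes up to 29 independent clinical variables", and "the widely-used rule of thumb of 10 x number of variables was adopted". That section also says that the variance-covariance matrix was not available at planning, so the correlation between these two predictors was not known to the authors either.

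The Discussion gives the intended use: "These are all data and analyses that could be included in routine clinical practice to better select patients likely to have RT response".

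**The concern.** Total dose is the number of fractions multiplied by the dose per fraction. The two terms can be told apart only as far as dose per fraction varies among patients with the same number of fractions. When both are in one model, each coefficient measures a contrast at a fixed value of the other, and the data may contain few such contrasts. Each standard error is then inflated.

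That would be a minor matter if the model were used whole. Here each coefficient has to reach significance alone before its variable enters the score. If the regimen is related to response, the two terms share the signal, both may miss the threshold, and the score and the report would carry nothing on regimen although the data hold the information. These are the only two terms in the primary model that describe the dose and fractionation of the RT.

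**Working it through.** **The plan's own figure.** 10 × 29 = 290, as stated under Power consideration. This point does not change that figure. Patients available after the stated loss of up to 20%: 600 × 0.8 = 480.

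**Assumptions.** The article gives no correlation, regimen mix or effect size, and no significance level for selection. I take two-sided 0.05, the roughly 60% response that the article expects, and a range of correlations r.

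**Step 1, general formula.** VIF = 1/(1 − r²). For an effect that lies wholly on one term and would have 80% power without the other, m = (1.96 + 0.84)/√VIF and power = Φ(m − 1.96) + Φ(−m − 1.96). Example, r = 0.9: VIF = 1/(1 − 0.81) = 5.26; m = 2.80/2.29 = 1.22; power ≈ Φ(−0.74) = 0.23.

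| r | VIF | Power (80% without the other term) |
|---|---|---|
| 0.5 | 1.3 | 68% |
| 0.7 | 2.0 | 52% |
| 0.8 | 2.8 | 39% |
| 0.9 | 5.3 | 23% |
| 0.95 | 10.3 | 14% |
| 0.98 | 25 | 9% |

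**Step 2, what r might be.** The mixes are illustrations only. Take 50% of patients with 1 fraction/8 Gy, 20% with 5/20 Gy and 30% with 10/30 Gy. The means are 4.5 fractions and 17 Gy, the variances 15.25 and 93, and the covariance 37.5. So r = 37.5/√(15.25 × 93) = 0.996 and VIF = 118. With only two regimens the points lie on a line, r = 1, and one term cannot be estimated.

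**Step 3, simulation.** 1,000 data sets per mix, n = 480, 60% response. The true effect is a log odds ratio of 0.29 per SD of the standardised sum of the two variables (odds ratio e^0.29 = 1.34), with no other covariates. The one-term model uses total dose alone; fractions enter as a count.

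| Assumed mix | r | VIF (count) | VIF (single/multiple) | Either of two terms p<0.05 | One term p<0.05 | Joint 2-df test p<0.05 |
|---|---|---|---|---|---|---|
| 3 conventional regimens | 0.996 | 118 | 7.8 | 6% | 88% | 79% |
| 5 regimens | 0.987 | 37.7 | 7.8 | 9% | 86% | 78% |
| 11 regimens, wide | 0.968 | 15.7 | 4.5 | 12% | 87% | 82% |
| Varied dose per fraction | 0.748 | 2.3 | 3.5 | 35% | 80% | 78% |

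A separate set of six mixes of 1, 5, 10 and 13 fractions gave VIF 15.4 to 118.2.

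**Step 4, sensitivity to effect size.** With a larger effect (odds ratio 1.5 per SD) lying wholly on one coefficient, SE = √(VIF/(480 × 0.6 × 0.4)) = √(VIF/115.2), and ln 1.5 = 0.405. Power is 0.99 at VIF 1, 0.82 at 2.3, 0.64 at 3.5, 0.34 at 8, 0.20 at 15 and 0.11 at 40. At the low end of the VIF range the loss is then modest; at the high end it is not.

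**Step 5, sign of the estimates.** In the simulated mixes, at least one of the two coefficients had the opposite sign in 29 to 88% of runs, but an opposite-signed coefficient was also significant in only 0.3 to 3.1%.

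**The case against.** The strongest objection is that strong collinearity is nowhere in the document. The study is multinational, several sites may be irradiated in one patient, and neither regimens nor coding are given. A reader might infer that fractions and total dose nearly determine each other. The article calls the RT standardised, which hints at few regimens but does not show it. This stands: the size is unknown, and Step 4 shows that the loss can be modest.

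Second, the information is not destroyed. A reader might conclude that the model cannot say whether regimen is related to response. That is wrong: a joint test of the same two terms finds the effect in 78 to 82% of simulated runs. Nor does collinearity by itself bias the full model's predicted probabilities. The harm comes from the selection rule, not from having both terms in the model.

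Third, a reader might fear that regimen would be scored with an arbitrary sign. Only significant variables are scored, and a significant opposite-signed coefficient arose in at most about 3% of runs, so this is not a likely outcome.

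Fourth, regimen is not the only treatment exposure in the model: other current oncological treatment, opioid dose and steroids are asterisked too.

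Fifth, diagnostics are planned, and collinearity rules are often left to an analysis plan. Diagnostics could well reveal the problem. But the article itself fixes the predictor list and the selection rule, and the one action it names, adding interaction terms, would not separate the two variables.

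Finally, it could be argued that a clinician-chosen regimen should earn no points in a score meant to select patients. That is a separate and debatable choice, and this point does not depend on it.

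**Conclusion.** The point holds as a conditional weakness in a stated analysis choice. Two descriptions of one prescription are entered separately and judged one coefficient at a time, so a real association between regimen and response can be dropped. Over the mixes simulated, detection was 6 to 35% under the stated rule, against 78 to 88% when the regimen was handled as one term or tested jointly. These figures rest on assumed mixes, 480 patients, 60% response, a 0.05 level, no other covariates and an effect shared between the two variables. A larger effect lying on one variable would lose less. Masking is the likely result if the correlation is about 0.9 or more and is moderate at 0.7 to 0.8. The base sample size of 290 is unaffected. The point is worth settling before the primary model is fitted, but it does not call the study as a whole into question.

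**What to change.** State one of two options in the primary analysis.

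1. Replace the two asterisked terms by one prespecified regimen variable derived from the recorded fractions and dose, with its coding given.
2. Keep both terms, but decide on them together with a joint 2-df likelihood ratio test, and carry both into the score or neither.

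Option 1 gave 80 to 88% detection and option 2 gave 78 to 82% in the simulated mixes. Option 2 costs a little power but does not require choosing a summary variable beforehand.

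Either is a sentence of analysis wording, uses data already collected, and changes neither treatment nor sample size. The downside is that separate effects of dose and fraction number are not individually reported; if the two are strongly correlated, the data could hardly separate them anyway. Reporting the observed cross-table of fractions by total dose would let readers see how far they can be separated.

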#### Blood samples

Standard clinical chemistry will be obtained at all visits and analyzed at the local laboratory in each study center. Full blood for genetic analyses is obtained at baseline and serum for analyses on biomarkers is obtained at all visits. The serum samples will be centrifuged at room temperature at 2200 g for 10 min, frozen within 1 hour and stored at − 80 degrees Celsius until analyses. A M*ultiplex cytokine assay* (Bio-Plex Pro™ Human Cytokine Plex-27 Assay, Bio-Rad Laboratories, Hercules, CA) will be carried out to analyse inflammatory biomarkers. Cytokines involved in bone remodelling will be analysed by EIAs using matched antibodies from R&D Systems. High-sensitivity CRP will be analysed on a MODULAR platform (Roche Diagnostics, Basel, Switzerland.) For patients where collection of blood samples at follow-up is not possible (i.e. due to travelling distance from study center), the clinical data are obtained, and participation is allowed without the collection of follow-up blood samples (Table 2).

**Table 2 Tab2:** Overview of blood samples obtained at all visits

Clinical chemistry	Hemoglobin, white blood cells, differential white cell count, platelets, creatinine, urea, bilirubin, potassium, sodium, chloride, total calcium, phosphate, magnesium, CRP, albumin, triglycerides, vitamin-D
Inflammatory biomarkers	High-sensitivity CRP, IL-1β, IL-1, IL-1ra, IL-2, IL-4, IL-5, IL-6, IL-7, IL-8/CXCL-8, IL-9, IL-10, IL-12 (p70), IL-13, IL-15, IL-17, basic fibroblast growth factor (bFGF), granulocyte colony-stimulating factor (G-CSF), granulocyte-macrophage colony-stimulating factor (GM-CSF), interferon-gamma (IFN-ɣ), eotaxin/CCL11, IFN-ɣ-inducible protein (IP-10)/CXCL10, MCP-1)/CCL2, MIP-1α/CCL3), MIP-1β/CCL4, regulated on activation, normal T-cell expressed and secreted (RANTES)/CCL5, TNF, platelet-derived growth factor (PDGF), and vascular endothelial growth factor (VEGF).
Biomarkers involved in bone remodelling	RANK-ligand (RANKL), Osteoprotegerin (OPG) and Notch Ligands: DLL1 and Periostin.

### Power consideration

The sample size is based upon the primary outcome; response to RT for pain [18]. The analyses plan includes up to 29 independent clinical variables (see previous sections for variables marked with an asterisk.) A full statistical estimate of sample size requires knowledge of the variance-covariance matrix, which was not available at the planning stage of this study. Therefore, the widely-used rule of thumb of 10 x number of variables was adopted. This reasoning resulted in a sample size of 290. Based upon experience, interactions will arise which increases the needed number of patients, and up to 20% of patients were expected to be lost to follow-up. To account for this, the number of needed patients was set to 600. The original protocol plan was to include a validation sample of 1/3 of patients resulting in a total number of 1000 included patients. But because of slow recruitment, we had to close the study after 600 recruited patients, and the analyses will therefore be performed without the planned validation sample.

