## Abstract

**Background:**

Radiation therapy (RT) results in pain relief for about 6 of 10 patients with cancer induced bone pain (CIBP) caused by bone metastases. The high number of non-responders, the long median time from RT to pain response and the risk of adverse effects, makes it important to determine predictors of treatment response. Clinical features such as cancer type, performance status and pain intensity, and biomarkers for osteoclast activity are proposed as predictors of response to RT. However, results are inconsistent and there is a need for better predictors of RT response. A similar argument can be stated for the development of cachexia; there are currently no predictors that can identify patients who will develop cachexia later in the cancer disease trajectory. Experimental and preclinical studies show that pain, depression and cachexia are related to inflammation. However, it is not known if inflammatory biomarkers can predict CIBP, depression or development of cachexia.

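### The 10-per-variable rule is applied to all patients rather than to non-responders, so 290 (and 600 enrolled) falls short of the plan's own rule for a 29-variable logistic model

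*Protocol article*

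**What the plan says.** The Power consideration section explains that the covariance structure needed for a formal calculation was not available, and continues: "the widely-used rule of thumb of 10 x number of variables was adopted". The number of variables is given as "The analyses plan includes up to 29 independent clinical variables", with a pointer to the asterisked items under Clinical variables. The conclusion is "This reasoning resulted in a sample size of 290". The section then says that interactions will raise the requirement and that "up to 20% of patients were expected to be lost to follow-up", and ends: "To account for this, the number of needed patients was set to 600". It also says that the planned validation sample was given up because recruitment was slow.

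Under Outcome and statistical analyses, research question 1 makes the primary endpoint a yes/no response. Deaths before the 3-week assessment count as non-response, and patients with missing outcome data are left out. The model is set out as "Clinical variables (see previous chapter) and CRP will be included in a multivariate logistic regression model", adjusted for study centre, with interactions added where diagnostics call for them. A response score is then built from the significant variables.

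On the expected response, research question 2 describes radiotherapy as "expected to give pain relief in about 60% of the patients". The Abstract and the Discussion give the same figure.

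**The concern.** In a logistic regression, the information about the coefficients is limited by the smaller of the two outcome groups. The usual 10-per-variable rule is therefore stated in events of the rarer kind. The power paragraph multiplies 10 by the number of variables and reads the product as patients. It uses neither the response rate nor the expected number of non-responders.

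The paragraph is the only justification given for the size of the primary model. If the unit is wrong, a reader will believe the data support more unpenalised predictors than the adopted rule allows. Too many parameters for the rarer group means overfitted coefficients, unstable selection of significant variables and optimistic predictions. That matters here because a response score will be built from the selected variables and there is no validation sample to expose the optimism.

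**Working it through.** **Inputs.** Power consideration: 29 variables (an upper limit), 10 per variable, 20% loss (an upper limit), 600 enrolled. Outcome and statistical analyses: about 60% response, so about 40% non-responders. Clinical variables: asterisked items, counted by hand. Assumption: the 60% quoted for pain relief applies to the primary endpoint among evaluable patients.

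**The plan's own figure.** 10 × 29 = 290, which reproduces exactly. Loss alone would raise it to 290 / 0.8 = 362.5, or 363. The 600 leaves 600 × 0.8 = 480 evaluable, so the allowance for interactions is implicitly 480 − 290 = 190 evaluable patients. No figure for it is stated.

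**The same rule on the rarer outcome.** With response rate r and p variables:

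- non-responders or responders per variable = evaluable N × min(r, 1 − r) / p
- evaluable N needed = 10 × p / min(r, 1 − r); enrolled = that / 0.8

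For r = 0.60 and p = 29: 290 / 0.4 = 725 evaluable, and 725 / 0.8 = 906.25, or 907 enrolled.

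| Case | Evaluable | Rarer group | Per variable, 29 | Per variable, 24 |
|---|---|---|---|---|
| 290 patients, 60% response | 290 | 116 | 4.0 | 4.8 |
| 600 enrolled, 20% loss, 60% | 480 | 192 | 6.6 | 8.0 |
| 600 enrolled, no loss, 60% | 600 | 240 | 8.3 | 10.0 |
| 600 enrolled, 20% loss, 50% | 480 | 240 | 8.3 | 10.0 |
| 600 enrolled, no loss, 50% | 600 | 300 | 10.3 | 12.5 |
| 600 enrolled, 20% loss, 70% | 480 | 144 | 5.0 | 6.0 |

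A 50/50 split is the most favourable possible. With 480 evaluable, no response rate therefore reaches 10 for 29 variables; the best is 240 / 29 = 8.3. At 60% response, 480 evaluable support 192 / 10 = 19.2, or about 19 parameters.

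**Number of variables.** The Clinical variables section carries 24 asterisks. Adding CRP makes 25, which gives 192 / 25 = 7.7 with 20% loss and 240 / 25 = 9.6 with none. These ratios make no allowance for study centre, interactions or extra category levels.

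**Early deaths.** Deaths before 3 weeks stay in the analysis as non-responders. As an illustration, assume that 5% of the 600 die early and that these 30 are part of the 20% loss. Evaluable patients are then 480 + 30 = 510 and non-responders 192 + 30 = 222. That is 222 / 29 = 7.7 per variable, or 222 / 24 = 9.3. In the extreme case where all 120 losses are early deaths, the 288 responders (480 × 0.6) become the rarer group, and 288 / 29 = 9.9 is still below 10.

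**The case against.** Several points on the other side are fair.

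- Ten per variable is only a heuristic, and missing it does not make the model impossible to fit. This stands: the finding is that the plan misapplies the rule it chose.
- Both 29 and 20% are upper limits, and early deaths add non-responders. This also stands. With 24 variables the rule is met exactly at 60% response with no loss, or at a 50% split with 20% loss. Neither case leaves room for centre or interactions.
- Recruitment is closed at 600, and the article openly discloses the loss of the validation sample. True, but the claim about what 600 supports, and the size of the model, can still be corrected.

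A reader might also infer stronger faults that the article does not support.

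- That interactions were ignored: the power paragraph does allow for them, though without a figure.
- That all clinical variables and every Table 2 marker enter one model: research question 1 screens the markers for detectability and variability and models them separately. Only significant terms are carried into an integrated model, and only if appropriate.
- That complete and partial response rates in the Background can be added to give a much smaller non-responder group: this conflicts with the 60% the plan itself uses.
- That CRP and category levels were certainly left out of the 29: the surplus of five over the asterisks could be those terms. The article does not say.

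**Conclusion.** The concern holds as a misapplied rule, not as an arithmetic slip, since 10 × 29 is indeed 290. On the basis that applies to a logistic model, and at the plan's own 60% response, 600 enrolled gives 6.6 non-responders per variable for 29 variables after 20% loss and 8.3 with no loss. At 60% response the requirement would be 725 evaluable, about 907 enrolled. The 600 was meant to cover interactions and loss as well, yet it falls short for 29 main effects alone unless both the loss and the response split are more favourable than the plan expects.

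The exact ratio depends on three things the article leaves open: how many parameters are really in the model, how much loss occurs, and how many early deaths are counted as non-responders. The direction does not change over the plan's stated values. Separately, 29 and the 24 asterisks do not agree.

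**What to change.** 1. Restate the power paragraph on the rarer outcome: about 192 expected non-responders, supporting about 19 regression parameters at the adopted rule, with the range for lower loss and for early deaths.
2. Reconcile 29 with the 24 asterisked variables, and say whether CRP and the levels of categorical variables such as tumour diagnosis are included.
3. Before outcomes are analysed, either cut the candidate parameters to that budget or fit the full list with penalised logistic regression (ridge or lasso). How centre enters and whether interactions are examined can stay with the analysis plan, but in an unpenalised model their parameters count against the budget.

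The cost is a change of wording and of the analysis plan, with no added patients. The downside is that the stated adequacy becomes less favourable and fewer predictors can be examined without penalisation.
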